## Abstract

**Background:**

People living with Parkinson’s disease experience progressive motor and non-motor symptoms, which negatively impact on health-related quality of life and can lead to an increased risk of hospitalisation. It is increasingly recognised that the current care models are not suitable for the needs of people with parkinsonism whose care needs evolve and change as the disease progresses. This trial aims to evaluate whether a complex and innovative model of integrated care will increase an individual’s ability to achieve their personal goals, have a positive impact on health and symptom burden and be more cost-effective when compared with usual care.

**Methods:**

This is a single-centre, randomised controlled trial where people with parkinsonism and their informal caregivers are randomised into one of two groups: either PRIME Parkinson multi-component model of care or usual care. Adults ≥18 years with a diagnosis of parkinsonism, able to provide informed consent or the availability of a close friend or relative to act as a personal consultee if capacity to do so is absent and living in the trial geographical area are eligible. Up to three caregivers per patient can also take part, must be ≥18 years, provide informal, unpaid care and able to give informed consent. The primary outcome measure is goal attainment, as measured using the Bangor Goal Setting Interview. The duration of enrolment is 24 months. The total recruitment target is *n*=214, and the main analyses will be intention to treat.

**Discussion:**

This trial tests whether a novel model of care improves health and disease-related metrics including goal attainment and decreases hospitalisations whilst being more cost-effective than the current usual care. Subject to successful implementation of this intervention within one centre, the PRIME Parkinson model of care could then be evaluated within a cluster-randomised trial at multiple centres.

## Introduction

### Background and rationale {6a}

Parkinson’s disease (PD), the most common cause of parkinsonism, is a chronic neurodegenerative disorder that affects approximately 1% of the UK population aged over 60 years [1]. PD disproportionately affects older adults and it is estimated that the global prevalence will increase in the coming decades, in part due to growth in the ageing population, in part also due to cumulative effects of toxic chemicals in our environment [2]. Although there is significant heterogeneity in both the symptoms and the rate of disease progression in people with PD, the care pathways that are in place are not tailored towards individual phenotype and needs [3, 4]. Current care systematically lacks continuity and is not patient-led, and issues that people with PD and their caregivers face are often identified too late and managed reactively, instead of taking a more proactive approach [5]. There is also a greater need amongst people with PD to self-manage where active monitoring of their own physical and psychological status could be undertaken and appropriate decisions made. Additionally, a more coordinated and integrated approach between the multidisciplinary team members that manage the patient is required [6].

Integrated models of care have been developed for other chronic conditions including diabetes and coronary heart disease. The evidence is clear that self-management and behaviour change programmes improve outcomes [7]. It is evident therefore that novel and innovative models need to be established and robustly tested in people with PD given the high and fast-growing prevalence of this condition. A new model, called PRIME Parkinson (Proactive and Integrated Management and Empowerment), has been developed and is designed to manage issues proactively, deliver cohesive, multidisciplinary care, and empower patients and their caregivers towards greater self-management [8, 9]. Whilst this approach seeks to tackle issues in the delivery of healthcare, there is uncertainty as to whether it improves outcomes for patients and their caregivers or if it is cost-effective within a UK setting. The aim of this randomised controlled trial (RCT) of a complex intervention [10] is to determine if the PRIME Parkinson model of care will augment an individual’s ability to achieve their personal goals, and positively impact health and wellbeing in people with parkinsonism and their caregivers. Attainment of personal goals has been chosen as the primary outcome measure to reflect the highly heterogenous population that are being targeted with this individualised treatment approach.

### Objectives {7}

To determine if PRIME Parkinson care can improve the primary outcome of goal attainment, and secondary outcomes (encompassing measures across multiple domains of health-related quality of life and symptom burden), decrease hospitalisations, and be cost-effective in people with parkinsonism when compared with usual care.Through mixed methods process evaluation, to explore how and to what extent the intervention was implemented and how and why the intervention was or was not beneficial.To determine the effect of PRIME Parkinson care versus usual care on those caring for, living with, or supporting a person with parkinsonism.

### Trial design {8}

A single-centre, randomised controlled trial of PRIME Parkinson care versus usual care.

## Methods: participants, interventions and outcomes

This protocol is reported in accordance with SPIRIT (Standard Protocol Items: Recommendations for Interventional Trials) guidance.

### Study setting {9}

This trial will be delivered at a single centre, the Research Institute for the Care of Older People, the Royal United Hospitals Bath NHS Foundation Trust, in South West England. Participants will be recruited from the local geographical catchment area.

### Eligibility criteria {10}

The eligibility criteria for trial participation are shown in Table 1. Where there is uncertainty about the diagnosis, a decision will be reached from discussion and consensus between the patient’s usual treating clinician and the PRIME trial team. Patients must be able to provide informed consent to participate or where unable to do, there must be availability of a close friend or relative to act as a personal consultee. We have designed this complex intervention trial to ensure inclusion of under-represented groups with particular regard for those with cognitive impairment or dementia in order to maximise the generalisability of the findings. Cognitive impairment is common in people with parkinsonism [11], and this group is often precluded from participating in clinical research [12, 13]. Recognising the physical and psychological negative impact that caregivers may experience [14, 15], up to three informal caregivers, per person with parkinsonism, will also participate (Table 1).

**Table 1 Tab1:** Inclusion and exclusion criteria for patients and caregivers

Group	Criterion	Definition
**Patients, inclusion**	Age	≥ 18 years
	Diagnosis of parkinsonism	Includes idiopathic Parkinson’s disease, progressive supranuclear palsy, corticobasal degeneration, multisystem atrophy, dementia with Lewy Bodies, vascular parkinsonism or primary progressive freezing of gait
	Location	Be resident within the geographical catchment area of the trial site
	Willingness	Be willing to participate
**Patients, exclusion**	Cause of parkinsonism	Drug, infection or toxin induced parkinsonism
	Capacity	Lack capacity to participate and do not have anyone who can be a consultee to provide advice regarding the patient’s wishes and views
	Decision of clinician	Current medical, cognitive or psychosocial issue or co-enrolment in other study that, in the opinion of the site investigator, would interfere with adherence to study requirements
**Caregivers, inclusion**	Age	≥ 18 years
	Provision of care	Provide informal care or support for a patient with parkinsonism
	Willingness	Be willing to participate
	Capacity	Have the ability to provide informed consent to participate
**Caregivers, exclusion**	Formal care	Professional caregivers who are paid to deliver care
	Person with parkinsonism not participating	Unwillingness or ineligibility of person for whom they provide care

### Who will take informed consent {26a}

Written informed consent will be taken from the patient and their caregiver(s), if relevant, at the baseline visit (Visit 1) by a member of the trial team. If, prior to Visit 1, there is indication from speaking to the patient, caregiver or a family member that the patient may lack capacity to consent, a capacity assessment will be conducted by phone by a trained member of the trial team to assess their ability to make a decision about research participation according to the Mental Capacity Act 2005 [16]. If the patient is unable to provide informed consent to participate, a close family member or friend who can act as a personal consultee will be identified and the patient’s prior wishes will be explored. If it is their view that the patient would wish to take part, they will be asked to accompany the patient to Visit 1 to complete a consultee declaration form. The personal consultee does not need to remain for the entirety of Visit 1 if a different caregiver or supporter can attend with the patient. If Visit 1 is held remotely over the phone or by videocall, the patient and consultee, as appropriate, will be asked to complete the consent form and/or consultee declaration form prior to the virtual visit and return it to the trial team by post. Patients are randomised to the intervention or the control arm at Visit 1.

### Additional consent provisions for collection and use of participant data and biological specimens {26b}

No biological specimens will be collected for storage.

## Interventions

### Explanation for the choice of comparators {6b}

The two arms of the trial are:Intervention arm—PRIME Parkinson model of care plus usual careControl arm—usual care

### Intervention description {11a}

The intervention is the PRIME Parkinson model of care which will be delivered by a multidisciplinary team including trained research staff, doctors and allied health care professionals, such as physiotherapists, occupational therapists and others. Patients in the intervention arm will continue to be offered usual care including follow-up with their regular Parkinson’s specialist. Contacts may take place face-to-face, in a patient’s home or another suitable location, remotely by phone or videocall. The intervention is a multi-component model of care comprising four components as follows [9]:

#### Care management

Patients will be assigned a care manager who will co-ordinate care and facilitate cooperation between those involved in their care [6]. Patients, their caregivers, general practitioner and secondary care teams will also have access to a ‘single point of access’ phone number and the call will be triaged by the study team towards the most appropriate PRIME team member. At Visit 1, patients will take part in a goal-setting interview and will be provided with a Personalised Care Plan where their priorities, current concerns and plan for how to address the goals identified will be documented.

#### Empowerment of patients and caregivers

This component encourages self-management of the condition. Patients and their caregivers will be provided with and supported to access relevant resources. They will be invited to attend group education workshops on topics such as medication management and nutrition. They will be signposted towards existing resources including information booklets, referral to third sector organisations, peer support and befriending services. Although patients who receive usual care can continue to access existing resources directly, intervention patients and their caregivers will be proactively signposted towards those which are most relevant to their needs and phenotype [17].

#### Empowerment of healthcare professionals

The PRIME multidisciplinary care team will comprise a multidisciplinary team of clinicians. The core team are supported to develop specialist clinical knowledge and skills to augment the successful delivery, the success of which will be evaluated of the PRIME intervention [18].

#### Development of specific IT infrastructure

A bespoke secure IT platform will be utilised which allows the intervention team to document their contacts with, and management plan for participants, and enhance communication to aid the coordination of care. It will also be accessible to patients themselves, as well as their caregivers. Patients and caregivers will be able to access educational materials which are relevant to the patient’s and the caregiver’s needs.

#### Control arm—usual care

Patients allocated to the usual care arm will continue to receive their usual care which includes scheduled follow-up by a movement disorder clinician or Parkinson’s nurse specialist. This is generally every 6 months and alternates between the clinician and the nurse. They may also have access to non-specialist physiotherapy and occupational therapy input, and access to resources such as those provided by Parkinson’s UK.

### Criteria for discontinuing or modifying allocated interventions {11b}

A patient and/or caregiver can choose to engage or not in any of the offered interventions in the active arm. Regardless of engagement and compliance with either the intervention and/or the assessments, participants will be encouraged to complete trial-related assessments. Enrolled participants from either arm can withdraw from the trial at any stage without prejudicing their usual care. Data collected until the point of withdrawal will be retained and used in the final analysis.

### Strategies to improve adherence to interventions {11c}

Engagement with the intervention will be monitored using process measures relating to each of the components of the PRIME Parkinson model of care and the intervention iteratively changed to improve adherence. Process measures will include data on usage of the single point of access, including source of the call, outcome of the triage process and action taken by the team; attendance at group educational sessions and engagement with educational materials; attendance at, and duration of, multidisciplinary team meetings; and the frequency with which the personalised care plan is reviewed and updated. The intervention is individualised and designed in conjunction with people with parkinsonism to maximise adherence.

### Relevant concomitant care permitted or prohibited during the trial {11d}

Usual care will continue to be offered to those patients in the intervention arm.

### Provisions for post-trial care {30}

Patients in the intervention arm will return to usual care at the end of the 24-month intervention period. Patients and caregivers can receive compensation for travel costs only.

#### Public and patient involvement

Public and patient involvement (PPI) representatives were included in the developmental stages of this protocol. They continue to be integrated in the study through providing feedback on patient facing documents including the participant information brochures, consent forms and the personalised care plan.

### Outcomes {12}

The primary outcome for patients is goal attainment which will be measured prospectively at 3 monthly intervals using the Bangor Goal-Setting Interview [19]. The primary outcome measure for patients will be analysed whereby an overall, unweighted mean rating for attainment across goals will be calculated at each evaluation point by dividing the sum of the ratings for all goals set by the participant by the number of goals set. Goal attainment will be additionally analysed with goals weighted according to the importance ratings stated by the participant at the goal-setting interview conducted at Visit 1. The primary outcome for caregivers is care-related quality of life measure using the Carer Experience Scale [20]. Outcome measures for patients and caregivers are described in Tables 2 and 3, respectively. A separate qualitative study will be carried out to explore the experiences of patients and caregivers recruited to the trial, and of hospital staff involved in the care of people with PD alongside staff involved in the delivery of the intervention. This will be reported separately.

**Table 2 Tab2:** Outcome measures for patients which will be measured at baseline, 12 and 24 months

Domain	Outcome	Measurement tool/method where one is available
**Primary outcome measure**	Goal attainment	Bangor Goal-Setting interview [19]
**Parkinson’s specific measures**	Parkinson’s disease assessment	MDS-Unified Parkinson’s Disease Rating Scale (MDS-UPDRS) [21]
	Non-motor symptom burden	MDS Non-Motor Rating Scale (MDS-NMS)* [22]
	Parkinson’s-related quality of life	Parkinson’s Disease Questionnaire (PDQ-39)* [23]
**Health**	Fear of falling	Iconographical Fall Efficacy Scale (ICON-FES)-short version [24]
	Global impression of change	Patients’ Global Impression of Change (PGIC) Clinician Global Impression of Change (CGI-I)
	Frailty	SHARE-FI 75+ (Phenotypic frailty tool) [25] Pictorial fit frail scale* [26] Clinical frailty scale [27]
	Sarcopenia	SARC-F* and *SARC*-*CalF** [28]
	Malnutrition risk	Malnutrition Universal Screening Tool (MUST)
	Nutritional risk	Seniors in the community: risk Evaluation for Eating and Nutrition (SCREEN II)-14 item version* [29, 30]
	Delirium	4AT tool for delirium assessment [31]
**Physical performance**	Physical performance	Short physical performance battery (SPPB) Time up and go test (TUG)
	Physical activity	Incidental and Planned Exercise Questionnaire for the Usual week (IPEQ-WA)* [32]
	Endurance	Endurance measure (2-min walk test, 6-min walk for those who are sufficiently mobile)
	Gait	Single and dual task gait assessments
	Grip strength	Hand-held dynamometer
	Falls^#^	N/A
**Palliative measures**	Advance Care Plan data	N/A
	Palliative symptom burden	Edmonton Symptom Assessment System Scale for Parkinson’s Disease (ESAS-R-PD) [33] Palliative outcome score-symptoms-Parkinson’s Disease (POS-S-PD) [34]
	Presence of gold standard framework register	Hospice utilisation outside place of death
	Healthcare contacts with hospice and / or palliative care services	Use of anticipatory medication
**Social**	Loneliness/social isolation	3-item Revised-UCLA Loneliness Scale plus a single item direct measure of loneliness [35]
	Social participation	English Longitudinal Study of Ageing questions (ELSA)* [36]
	Perceived social support	Multidimensional scale of perceived social support [37]
	Coping strategy	BriefCOPE [38]
	Acceptance of illness	Acceptance of illness scale [39]
	Capability	ICEpop CAPability measure for Older people (ICECAP-O)* [40]
	Patient activation	Patient Activation Measure (PAM) [41]
**Economic measures**	Health-related quality of life	EuroQoL 5D-5L health status questionnaire (EQ-5D-5L)* [42]
	Mortality^#^	N/A
	Healthcare events (including elective & unplanned admissions, emergency department attendances, outpatient appointments, primary care contacts, investigations and prescriptions, discharge destination)	Captured from hospital and GP records and participant self-report
**Process measures**	Frequency of Parkinson’s follow-up and referral to, and review, by allied health professionals (intervention and control arms)	N/A
	Frequency and type of engagement with PRIME Parkinson care (intervention arm)	N/A
	Experience of holistic patient-centred care	Patient Assessment of Chronic Illness Care measure (PACIC) - 26 item [43, 44]

*=outcomes that will be completed by a representative who knows the patient well, where the patient cannot self-complete; #=outcome measures which will also be assessed at 3, 6, 9, 15, 18 and 21 months. The following parameters will be assessed at baseline and/or at 12/24 months but are not outcome measures per se: fracture risk using FRAX* [45] and/or QFracture* [46] with bone densitometry where required; habitual dietary intake using the European Prospective Investigation into Cancer Food frequency questionnaire* [47]; comorbidity using Cumulative Illness Rating Scale-Geriatrics [48]; cognition using Montreal Cognitive Assessment (MoCA) [49]. Place and date of death, where applicable, will also be captured

**Table 3 Tab3:** Outcome measures for caregivers which will be measured at baseline, 12 and 24 months

Domain	Outcome	Measurement tool/method, where one is available
**Caregiver measures**	Care-related quality of life	Carer Experience Scale (primary outcome) [20]
	Caregiver quality of life (PD-specific)	Parkinson’s Disease Questionnaire for carers (PDQ-carer) [50]
	Caregiver burden	Zarit Burden Interview [51]
	Caregiver activation level	Patient Activation Measure 13 UK (CG-PAM) [41]
	Caregiver coping strategy	BriefCOPE [38]
	Care (including relationship to recipient, living with recipient, intensity of caring, duration of care duties, tasks of caring)	N/A
**Health**	Frailty	Survey of Health, Ageing, and Retirement in Europe (SHARE-FI) 75+ [25]
	Sarcopenia	SARC-F and *SARC*-*CalF* [28]
	Malnutrition risk	Malnutrition Universal Screening Tool (MUST)
	Nutritional risk	Seniors in the community: risk Evaluation for Eating and Nutrition (SCREEN II)-14 item version [29, 30]
**Performance**	Physical performance	Short physical performance battery (SPPB) Time up and go test (TUG)
	Physical activity	Incidental and Planned Exercise Questionnaire for the Usual week (IPEQ-WA) [32]
	Grip strength	Hand-held dynamometer
**Social**	Loneliness/social isolation	3-item Revised-UCLA Loneliness Scale plus a single item direct measure of loneliness [35]
**Economic measures**	Caregiver costs	The Caregiver Indirect and Informal Case Cost Assessment Questionnaire [52]
**Process measures**	Frequency and type of engagement with PRIME Parkinson care (intervention arm)	N/A

The following parameters will be assessed at baseline and/or at 12/24 months but are not outcome measures per se: fracture risk using FRAX* [45] and/or QFracture* [46]; habitual dietary intake using the European Prospective Investigation into Cancer Food frequency questionnaire* [47]

#### Rationale for primary outcome

Given the heterogeneity of parkinsonian conditions, goal attainment was chosen as the primary outcome measure because it is patient-centred, meaningful to participants and not focused on a single symptom or domain. Goal-based approaches have been used successfully in frail older adults [53] and people with multiple sclerosis [54]. The Bangor Goal-Setting Interview has been applied in a multicentre trial of cognitive rehabilitation in people with early-stage dementia and has been shown to be feasible for use in people with Parkinson’s dementia and dementia with Lewy Bodies [55, 56].

### Participant timeline {13}

The duration of the intervention is 24 months.

### Sample size {14}

In the GREAT trial, the mean score for goal attainment at baseline was approximately 3.5 (SD 1.6) [55]. To detect a standardised effect size of 0.5 between groups (regarded as a moderate effect size [57] with 90% power, we would need 85 in each group. To allow for 20% attrition, this sample size has been inflated to give a total sample size of 214, with 107 patients in each arm. In terms of caregivers, a previous study has estimated that up to 80% of people with moderate to advanced Parkinson’s have an informal caregiver [58]. If 80% of the 214 recruited patient participants have an informal caregiver and 70% of these agree to take part, this would result in 120 caregiver participants (60 in each arm). With this number of caregiver participants, we could detect a difference of half a standard deviation in the primary outcome measure with 80% power and at a 5% significance level. This is equivalent to a 9 point difference in the CES index score, based on Rand et al. who reported a mean CES index score of 68.70 with a standard deviation of 17.78 amongst carers of adults using social care support in England [59]. We will have slightly greater power because we will recruit up to 3 caregivers per patient, although these will not be independent observations

Patients will be recruited predominantly through three routes. The first is where they will have expressed written interest in hearing about further research on a consent form through participating in other research studies. Secondly, they may be identified by the trial team from current hospital admissions or clinic lists. Thirdly, they may hear about the trial through local advertising or on social media. Potential participants will be sent an invitation pack containing a letter of invitation, a Patient Information Brochure, a pre-paid reply slip and a consent form, which is for information only. It will also include the equivalent documents for a potential caregiver who may wish to take part. If the team has not heard from the potential participant within 2 weeks of posting the invitation pack to them, they will receive a phone call and all questions will be answered. Potential participants and caregivers who indicate that they are interested in taking part, either by phone or by posting back the reply slip(s), will receive an appointment letter for Visit 1 with the relevant questionnaire booklet or a link to electronic questionnaires, depending on their preference.

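### The 80% caregiver power is a figure before any loss to follow-up; after loss it falls to roughly 68–73% with one caregiver per family

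*Protocol article*

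**What the plan says.** All the figures are in the protocol article, Sample size {14}. For patients, 85 per arm are required, and the text continues: "To allow for 20% attrition, this sample size has been inflated to give a total sample size of 214". That gives 107 per arm.

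The caregiver count starts from the inflated total: "If 80% of the 214 recruited patient participants have an informal caregiver and 70% of these agree to take part", there would be 120 caregivers, 60 per arm. The power claim follows: "With this number of caregiver participants, we could detect a difference of half a standard deviation in the primary outcome measure with 80% power", at a 5% significance level. On the CES it is expressed as follows: "This is equivalent to a 9 point difference in the CES index score". The source cited for this "reported a mean CES index score of 68.70 with a standard deviation of 17.78".

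The caregiver rate is taken from a previous study which estimated that "up to 80% of people with moderate to advanced Parkinson’s have an informal caregiver". The paragraph closes by expecting a slight gain in power from recruiting up to three caregivers per patient, and concedes that these are not independent. It gives no figure for that gain and makes no allowance for caregiver attrition.

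Two other sections matter. Table 3 schedules the CES at baseline, 12 and 24 months. Statistical methods {20a} tests at 24 months first and adapts that approach to caregiver outcomes.

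**The concern.** One paragraph treats the two samples differently. It expects to lose a fifth of the patients and recruits more to compensate. It then derives the caregiver number from the enlarged recruitment figure and computes power as though none of those caregivers were lost over 24 months.

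The effect on caregivers is one of the three stated objectives, and the CES is the named caregiver primary outcome. If the caregiver comparison shows no clear difference, a reader may rely on the 80% power claim to argue that a 9-point effect has been ruled out. The trial would be less able to support that argument than the text suggests.

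**Working it through.** **Inputs.** From Sample size {14}: 214 patients; 80% with a caregiver; 70% uptake; difference 0.5 SD; SD 17.78; 5% level; 20% attrition, stated for patients. From Allocation sequence generation {16a}: expected 1:1 allocation. Sidedness is not stated, so two-sided is assumed. The patient figure of 85 per arm (0.5 SD, 90% power) reproduces on a two-sided 5% basis, which supports that choice.

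**Reproducing the plan's figure.** 214 × 0.8 × 0.7 = 119.84, so 120 caregivers, 60 per arm. The normal approximation is power = Φ(d·√(n/2) − 1.96).
- n = 60, d = 0.5: 0.5 × √30 = 2.739; 2.739 − 1.960 = 0.779; Φ = 78.2%.
- The t-test (noncentral t, 2n − 2 degrees of freedom) gives 77.5%.
- Using 9 points, d = 9/17.78 = 0.506: 79.2% (normal) or 78.5% (t-test).

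The stated 80% is therefore a rounded value for 60 analysed per arm. Strictly, 80% needs 63 per arm (normal) or 64 (t-test).

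**Allowing for loss.** One caregiver per family, d = 0.5:

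| Caregiver loss (assumed) | Analysed per arm | Power, t-test | Power, normal |
|---|---|---|---|
| 0% | 60 | 77.5% | 78.2% |
| 10% | 54 | 73.1% | 73.8% |
| 15% | 51 | 70.6% | 71.4% |
| 20% | 48 | 67.9% | 68.8% |
| 25% | 45 | 65.0% | 66.0% |

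**Detectable difference at 20% loss.** Normal approximation: (1.960 + 0.842) × √(2/48) = 0.572 SD; 0.572 × 17.78 = 10.2 points. By t-test it is 0.578 SD; 0.578 × 17.78 = 10.3 points.

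**Extra caregivers per family.** With mean family size m and intraclass correlation ρ, the effective number per arm is n·m / (1 + (m − 1)ρ), taking families as equal in size. Starting from 48 families per arm (m and ρ are assumed, since the document gives neither):
- m = 1.1, ρ = 0.5: 52.8/1.05 = 50.3; power 69.9% (t-test), 70.8% (normal).
- m = 1.1, ρ = 0.2: 52.8/1.02 = 51.8; power 71.2%, 72.0%.
- m = 1.25, ρ = 0.5: 60/1.125 = 53.3; power 72.5%, 73.3%.
- m = 1.25, ρ = 0.2: 60/1.05 = 57.1; power 75.5%, 76.2%.

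The range is about 70–76%. To reach 64 effective caregivers per arm, m would have to be about 1.33 at ρ = 0, 1.56 at ρ = 0.3 and 2.0 at ρ = 0.5.

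**Sensitivity to the caregiver rate.** Keeping 70% uptake and using the t-test, an assumed rate of 70% gives 71.8% power with no loss and 61.9% at 20% loss. An assumed rate of 60% gives 65.0% and 55.2%.

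**The case against.** The best defence is that the stated figure is not an arithmetic error. A reader might infer from 77.5% against 80% that the sum is wrong. It is not: the normal approximation with the protocol's own 9 points gives 79.2%. With no loss, a mean of about 1.14 caregivers per family closes the remaining gap even at an intraclass correlation of 0.5. That part of the defence stands.

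Second, a reader might infer that 68% is the power on the trial's own terms. It is not. The 20% is given for patients only. The document does not say what happens to caregiver follow-up when a patient dies or withdraws, so it does not establish that caregiver loss is at least as high. The 68% also assumes one caregiver per family, whereas up to three may join. This is why a range of loss rates and family sizes is needed. It does not rescue 80%: a 10% loss already gives 73%, and modest extra recruitment within families leaves power below 80% at 20% loss.

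Third, a reader might call 80% × 70% an upper bound on caregiver numbers. The document does not support this. Only the 80% is cited as a maximum, the 70% uptake is simply assumed, and extra caregivers could take the count above the product. The count is also worded conditionally and its source is disclosed. What remains is that a maximum from moderate to advanced disease serves as the working rate in a trial whose minimisation categories include Hoehn and Yahr stages 1–2. The expected stage mix is not given, so the size of any shortfall is unknown.

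Fourth, adjusting for baseline CES could recover power. At an assumed correlation of 0.5, 48 per arm would give about 81% (normal approximation). However, Statistical methods {20a} names only age and Hoehn and Yahr stage as covariates, so the stated power cannot rely on it. Nor does the planned imputation of missing data in general restore lost information.

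Finally, the trial is sized on the patient outcome, and confidence intervals are promised, which limits over-reading of a null result. Both points hold and bear on severity.

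**Conclusion.** The concern holds with moderate severity. The caregiver power is a before-attrition figure presented without that qualification, beside a patient calculation that does allow for attrition. For 0.5 SD it is about 78% with no loss, 73% at 10%, 71% at 15% and 68% at 20%, with one caregiver per family. At 20% loss it is about 70–76% with modest extra caregivers, and the 80%-detectable difference with one caregiver per family is about 0.58 SD.

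These results assume a two-sided 5% test, 1:1 allocation and no baseline adjustment. The caregiver loss rates, family sizes and intraclass correlations are assumptions, not figures from the protocol. The patient sample size is correct as stated and is not affected.

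**What to change.** In Sample size {14}, restate caregiver power after attrition and name the assumed caregiver loss rate. If the patient rate is used, 120 × 0.8 gives about 96 families at 24 months. The text could then give about 68% power for 0.5 SD with one caregiver each and roughly 70–76% with modest extra caregivers (stating the assumed mean and intraclass correlation), or 80% power for about 0.58 SD (10.3 CES points) with one caregiver each. Showing 10% and 15% loss alongside would make the dependence on the assumption clear.

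Add a sentence that the 80% caregiver rate comes from a maximum reported in moderate to advanced disease and may be optimistic here. Do not label the 80% × 70% product an upper bound.

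The cost is rewording and a less favourable stated figure. No extra recruitment or change of design is needed.
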